## Abstract

**Background:**

Natural hazards are increasing in frequency and intensity due to climate change. Many of these natural disasters cannot be prevented; what may be reduced is the extent of the risk and negative impact on people and property. Research indicates that the 2019-2020 bushfires in Australia (also known as the “Black Summer Bushfires”) resulted in significant psychological distress among Australians both directly and indirectly exposed to the fires. Previous intervention research suggests that communities impacted by natural hazards (eg, earthquakes, hurricanes, and floods) can benefit from interventions that integrate mental health and social support components within disaster preparedness frameworks. Research suggests that disaster-affected communities often prefer the support of community leaders, local services, and preexisting relationships over external supports, highlighting that community-based interventions, where knowledge stays within the local community, are highly beneficial. The Community-Based Disaster Mental Health Intervention (CBDMHI) is an evidence-based approach that aims to increase disaster preparedness, resilience, social cohesion, and social support (disaster-related help-seeking), and decrease mental health symptoms, such as depression and anxiety.

**Objective:**

This research aims to gain insight into rural Australian’s recovery needs post natural hazards, and to enhance community resilience in advance of future fires. Specifically, this research aims to adapt the CBDMHI for the rural Australian context and for bushfires and second, to assess the acceptability and feasibility of the adapted CBDMHI in a rural Australian community.

**Methods:**

Phase 1 consists of qualitative interviews (individual or dyads) with members of the target bushfire-affected rural community. Analysis of these data will include identifying themes related to disaster preparedness, social cohesion, and mental health, which will inform the adaptation. An initial consultation phase is a key component of the adaptation process and, therefore, phase 2 will involve additional discussion with key stakeholders and members of the community to further guide adaptation of the CBDMHI to specific community needs, building on phase 1 inputs. Phase 3 includes identifying and training local community leaders in the adapted intervention. Following this, leaders will co-deliver the intervention. The acceptability and feasibility of the adapted CBDMHI within the community will be evaluated by questionnaires and semistructured interviews. Effectiveness will be evaluated by quantifying psychological distress, resilience, community cohesion, psychological preparedness, and help-seeking intentions.

**Results:**

This study has received institutional review board approval and commenced phase 1 recruitment in October 2022.

**Conclusions:**

The study will identify if the adapted CBDMHI is viable and acceptable within a village in the Northern Tablelands of New South Wales, Australia. These findings will inform future scale-up in the broader rural Australian context. If this intervention is well received, the CBDMHI may be valuable for future disaster recovery and preparedness efforts in rural Australia. These findings may inform future scale-up in the broader rural Australian context.

**International Registered Report Identifier (IRRID):**

DERR1-10.2196/53454

## Introduction

### Background

Due to climate change, natural hazards are increasing in frequency and intensity in Australia [1-4]. Natural hazards are defined as “threatening events, capable of producing damage to the physical and social space where they take place;” a natural hazard becomes a natural disaster when it has “a major impact on society and/or infrastructure” [5]. The 2019-2020 bushfires followed 3 years of intense drought in southern and eastern Australia and lasted nearly 12 months in some parts of the country. The bushfires burned an estimated 60 million acres, destroyed 6000 buildings (mostly homes), were responsible for the deaths of 462 people (33 fire-related and 426 from smoke inhalation) and contributed to the deaths of an estimated 3 billion animals [6-10]. The loss of land, displacement of people, and related myriad direct and indirect impacts of the 2019-2020 bushfires on millions of Australians were unprecedented [1]. Most communities were ill-equipped to cope with the scale of the fires.

The 2019-2020 bushfires resulted in significant psychological distress for both directly and indirectly exposed Australians [11]. Direct exposure to bushfires includes but is not limited to (1) loss of property, infrastructure, livelihood, and life; (2) impact of smoke inhalation on both physical and mental health; and (3) first-hand exposure to bushfire events. The negative impact of direct exposure on psychological well-being is extensively documented [12]. Indirect exposure to bushfires can occur through watching, listening, or reading news reports; witnessing someone being negatively impacted by bushfires; exposure to bushfire content through social media (eg, Instagram and Facebook); and discussions within the community about bushfire events. The impact of indirect exposure on psychological well-being mimics the experiences of those who are directly exposed [13]. Exposure to natural disasters in general can have long-lasting psychological consequences for individuals and their communities. On an individual level, a third to half of the exposed population can experience transient distress following the catastrophic event and a significant proportion may go on to develop chronic psychological conditions such as posttraumatic stress disorder (PTSD), depression, anxiety disorders, substance use, and suicidality [14-17]. Bushfire-specific research on the Ash Wednesday, Black Saturday, and Black Summer bushfires shows that these disorders and elevated psychological distress can persist for years or even decades, with distress directly proportional to bushfire proximity and severity [18-20]. These psychological consequences can be compounded upon repeated exposure to additional traumatic events or stressful life events [21-23].

The more physically prepared individuals are for natural disasters, the less physical and psychological harm they are likely to experience [24]. Yet, evidence suggests that communities and individuals often do not engage in disaster preparedness, even when sufficient education and resources are provided, and even in areas with past hazard exposure [24-27]. It has been found that individuals overestimate their level of preparedness. For example, a US study using national survey data found that 78% of respondents reported being prepared for disasters, whereas only 45% were actually prepared by objective assessment [28]. Preexisting mental health concerns and mental health consequences of prior disaster exposure may also interfere with disaster preparedness [29,30]. Research has shown that community members with poor mental health are less likely to have either an emergency plan or household disaster supplies [29]. Possible explanations for unpreparedness include cognitive and behavioral avoidances, commonly found in PTSD, and a sense of hopelessness, commonly found in depression, as well as procrastination and denial [30].

It is important to address barriers to disaster preparedness and enhance community resilience. Resilience in relation to natural disasters encompasses 3 common themes, first, the ability to absorb or accommodate the stressor or adverse event; second, the ability to recover and return to healthy levels of functioning (and not necessarily predisaster functioning); third, the ability to learn, adapt, or transform in response to disaster exposure [1,31-35]. The Australian Disaster Resilience Index was created to assess disaster resilience in Australia and it was found that most of the population of Australia lived in areas that were assessed as having “moderate” resilience for natural disasters, with “low” disaster resilience observed primarily in remote areas [1]. Most of the Australian population has a “moderate” ability to prepare for, absorb, and recover from natural disasters, and learn to adapt and problem solve. Natural hazards resulting in disasters have the potential to adversely affect the social cohesion of communities, which in turn, is linked with disaster resilience [31]. For example, disasters can rupture social networks within communities, thereby eroding existing social relationships and undermining social support [14,36]. Research also indicates that “cognitive social capital” matters, specifically, that lower levels of trust and a diminished sense of belonging are associated with poor mental health in disaster-affected communities [37]. Reciprocal relationships are important as limited social connections following disaster exposure have been associated with an increased risk of PTSD [38]. Taken together, this body of research underscores the importance of social support and community trust as protective factors associated with mental health in disaster-affected settings. Such factors can enhance or diminish community resilience.

Community-based initiatives that encourage collective involvement in mitigation, preparedness, response, and recovery can build resilience to natural hazards. It is preferable for local community leaders to collaborate with community members in developing local preparedness plans and related initiatives, collectively investing in resilience building [25]. Perhaps not surprisingly, studies suggest that disaster-affected communities often prefer the support of community leaders over that provided by health practitioners or other outsiders [39]. Collective community action associated with preparedness may also help to facilitate social cohesion, in turn having a positive impact on individual and collective well-being [40]. In summary, mental health, social cohesion, and disaster preparedness are important factors to address simultaneously through community-based programs to enhance resilience linked to disaster mitigation, preparedness, response, and recovery [30,40,41].

### Community-Based Disaster Mental Health Intervention

The Community-based Disaster Mental Health Intervention (CBDMHI) is an evidence-based approach to building community resilience in the face of natural hazards-related disasters. It has been implemented and evaluated with earthquake, hurricane, and flood-affected communities in Haiti and Nepal [25,30,42-44]. In addition to this initiative, it is in the process of being adapted and further tested in India, Turkey, and Syria for disaster-affected populations. The CBDMHI intervention aims to increase disaster preparedness, resilience, community cohesion, and social support (disaster-related help-seeking) and decrease mental health symptoms, such as depression, anxiety, and PTSD. A 3-day manualized version of the CBDMHI intervention is available in English, Haitian Kreyol, and Nepali. Previous research across 3 studies—2 randomized controlled trials and a matched cluster comparison—with disaster-affected communities in Haiti and Nepal support its effectiveness in increasing preparedness and social cohesion and decreasing mental health symptoms [25,30]. The intervention is specifically designed to be adaptable across contexts, cultures, and specific events. Community members are part of this adaptation process and are trained to cofacilitate the intervention. An initial consultation phase is a key component of this adaptation process.

### Study Objectives

This project aims to adapt the CBDMHI for the Australian bushfire context to increase community resilience in the face of ongoing bushfire risk. After adapting to the local context and for fires, the aim is to test the adapted intervention in a small-scale pilot study to assess the feasibility, acceptability, and effectiveness of the intervention in 1 rural community to inform potential scale-up for other disaster-affected communities in Australia.

## Methods

### Study Design

This research uses a sequential multimethods approach. This research is broken into 3 phases that are outlined in Figure 1. Phase 1 assesses the needs of the community to appropriately adapt the CBDMHI. Phase 1 consists of qualitative interviews (individual or dyads) with self-identifying members of a rural community in New South Wales, Australia, aiming to collect information regarding the community’s specific bushfire recovery needs. This process will include identifying themes related to disaster preparedness, social cohesion, and mental health. Phase 2 will involve additional discussion with key members of the community to refine the adaptation of the CBDMHI to specific community needs, building on phase I inputs. Local community leaders will be trained to cofacilitate the intervention in the community, which will be piloted in phase 3 of this study. Intervention acceptability, feasibility, and preliminary effectiveness will be assessed via pre- and postintervention individual mental health and community variables, as well as a 6-week follow-up. Acceptability will also be assessed postintervention.

Phase 1 will focus on community consultation and engagement. Community awareness events will be undertaken in the identified community prior to the commencement of the project, to promote the project and obtain community support (eg, phone calls with individuals in the community, face-to-face meetings in the local café to promote the project, and events with the local fire service). Phase 1 will primarily involve data collection through semistructured interviews with open-ended questions. The interviews will explore the impact of the 2019-2020 bushfires on community cohesion, community resilience, and well-being, as well as intervention preferences and perceived needs. Interviews will also focus on community preparedness for the 2019-2020 bushfires and what measures have been taken since that time to prepare for future fires. Questions will focus on current perceived needs related to the fires (at both the individual and community levels), primary stressors (past and current), and ongoing recovery. The data gathered will be used to inform the adaption of the CBDMHI to the local bushfire context.

In phase 2, the CBDMHI will be adapted to meet specific community needs. Data from phase 1 will be analyzed using inductive thematic analysis at the semantic level. The findings of the qualitative analysis will inform the adaptation of the CBDMHI. Adaptation based on community feedback may include the scenarios and group activities so that they are fire and community-specific; the content covered or focused on in the program (ie, the content will be selected to match stated community needs, for example, based on community feedback, there may be more of a focus on household level preparedness than on assisting extremely vulnerable groups within the community); and the length and timing of the program. The adaptation process may also necessitate additional content being added by clinical experts through the inclusion of additional psychoeducation or skills training to meet the community’s needs. Phase 2 will also involve additional discussion with key members of the community to further refine the adaptation of the CBDMHI to specific community needs. A local advisory group of community leaders and members will be formed for consultation during the adaptation process. Tailored materials for running the program in the local community will be developed.

**Figure 1 figure1:**
[figure not shown]
Study phases. CBDMHI: Community-Based Disaster Mental Health Intervention.

Phase 3 will involve piloting the adapted CBDMHI in the identified rural community. Phase 3 has been registered with the Australian New Zealand Clinical Trials Registry (ANZCTR) registration (ACTRN12623001023640). As part of this phase, the research team will train local and respected community leaders to administer or co-deliver the adapted CBDMHI. The intervention will consist of facilitated discussion, the space to share personal experiences, the establishment of peer support, the establishment of safety, and learning and practicing coping skills specifically for disaster-related distress. The intervention also provides practical training in disaster preparedness and response techniques that participants can use to support themselves and other community members during future hazards.

Phase 3 of the study will pilot the CBDMHI with residents of the affected community. The pilot intervention will use a pretest and posttest design to assess the acceptability of the intervention, as well as levels of psychological distress, resilience, coping, community cohesion, psychological preparedness, and help-seeking intentions following the intervention. Participants will complete measures before and after the workshop to assess the treatment effectiveness, as well as a 6-week follow-up. Due to the community setting and different availabilities of community members living in rural areas with property and farming obligations, random allocation is unlikely to be possible. Workshop participation and thus treatment implementation will, therefore, be a within-subject design with participants acting as their own controls. Drawing on the results from this study, a framework with Australian bushfire-specific materials will be developed and made available to facilitate broader implementation in the future to support recovery in other fire-affected Australian communities.

### Eligibility Criteria

Eligible participants are (1) persons aged 18 years and older, (2) who self-identify as a member of the bushfire-affected community in the Northern Tablelands region of New South Wales, (3) have lived and worked in the community during the fires and continue to reside within the bushfire-affected community, and (4) report having been directly or indirectly impacted by the 2019-2020 bushfires. Direct exposure includes having protected property or livestock; having been evacuated or relocated; experiencing loss of property, family, friends, and livestock; or having served as a firefighter or first responder, including in a volunteer capacity. Indirect exposure includes having heard recounts of the bushfires and their effects on the community secondhand. Ineligible participants are those not fluent in English or individuals who reside outside of the recruitment catchment area or are judged by clinicians as under the influence of alcohol or substances or have any other significant impediment to participation.

### Proposed Sample

The proposed sample for phase 1 will be determined through informational power [38]. Informational power is based on 5 concepts, aim, specificity, theory, dialogue, and analysis. When informational power is met the sample size will be determined.

The proposed sample for phase 3 is up to 20 participants, which is estimated as more than 15% of the total population of the target community. This target sample size is based on previous adaptations of the CBDMHI that used no more than 20 participants per intervention group [30,42]. This number is also in line with the recommended treatment group size for pilot studies [45].

### Recruitment

#### Phases 1 and 2

Participants will be recruited via advertising within the affected community, including community services, dining venues, and schools. The project will be advertised through partner organizations including the Rural Fire Service (RFS), community groups, and local social media pages, and through community engagement events held with the RFS.

Advertising materials and social media posts will be shareable, permitting recruitment through social contagion and snowball techniques, allowing maximum reach and community representation. The project team will contact individuals who registered their interest by phone and email to confirm eligibility and schedule interviews. Participation will not be incentivized.

#### Phase 3

This phase is open to any of the phase 1 participants, as well as any other persons residing or working in the catchment area (as per the eligibility criteria). Recruitment will occur through advertising within the target community including through the mentioned partner organizations, community services, community groups, and social media pages, and during local community events.

### Intervention

The CBDMHI is a manualized intervention that is culturally adaptable to disaster-affected communities [42]. Prior to the intervention, the research team will select and train local community leaders to deliver the modified CBDMHI. The CBDMHI will be modified in content and length based on the local communities’ needs and availability. The main objectives of the CBDMHI are to increase disaster preparedness (physical and psychological), community cohesion, resilience, and social support (disaster-related help-seeking), and decrease mental health symptoms, such as depression, anxiety, and PTSD.

### Outcomes

#### Measures

Participants in phase 3 of this research will complete a range of self-report measures prior to the intervention, at completion of the intervention, as well as a 6-week follow-up to assess durability. Measures will be collected via an anonymous survey completed in person with trained assessors pre- and postintervention and follow-up measures will be emailed along with reply paid envelopes. To link pre- and posttest questionnaire results, participants will be assigned a unique identifier.

#### Acceptability

Acceptability of the intervention will be measured using Likert-style and open-ended questions. The Likert-style questions will be scored using a 5-point Likert scale ranging from “strongly disagree” to “strongly agree,” with higher scores indicating higher acceptability. Open-ended questions (eg, “what did you like about the workshop?”) will also be used to measure acceptability. Participants will also be invited to take part in an optional follow-up semistructured interview to assess acceptability and perceived unhelpfulness.

#### Psychological Distress

Psychological distress will be measured using the Kessler Psychological Distress Scale (K10) [46]. The K10 is a 10-item questionnaire based on questions about anxiety and depressive symptoms that an individual has experienced in the previous 4 weeks. The K10 is based on a 5-point Likert scale, with responses ranging from “none of the time” to “all of the time.” The maximum score is 50 (indicating severe distress, likely to have a severe disorder), and the minimum score is 10 (indicating low distress, likely to be well). The K10 has demonstrated favorable discriminant validity and internal consistency [47].

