### Planned Data Analysis

Descriptive statistics will be provided for demographic data. Phase 1 community consultation interview data will be analyzed using thematic analysis [52] to explore participants’ physical, psychological, social, and environmental needs following the 2019-2020 bushfires. Inductive thematic analysis has been selected for this study as it is a useful qualitative approach for applied research designs [53]. Thematic analysis provides a flexible yet robust, systematic framework for coding data and has been used widely in the health sciences [53]. Data analysis will involve an iterative process including familiarizing oneself with the data, generating initial codes, searching for themes, reviewing themes, defining and naming themes, and producing the report [52,54].

One-way repeated measures ANOVAs will be performed for phase 3 outcome measures to identify any changes in pre- and postintervention outcomes, and whether those changes were maintained up to 6 weeks. Multilevel mixed models nested in time may also be used, as these analyses are more robust to missing data and can be used to model change trajectories over time. Where a change in score across time points is identified, the reliable change index will be used to assess the clinical significance of this change to provide further insight into the clinical meaningfulness and use of the program.

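### The K10 looks back 4 weeks but is repeated as the workshop ends, so for a short workshop the pre-to-post contrast is strongly attenuated; baseline to 6 weeks should be the K10 effect contrast

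*Protocol article*

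**What the plan says.** The Psychological Distress section states that the K10 rests on "questions about anxiety and depressive symptoms that an individual has experienced in the previous 4 weeks".

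The Measures section schedules all phase 3 scales "prior to the intervention, at completion of the intervention, as well as a 6-week follow-up to assess durability", with the first two surveys "completed in person with trained assessors pre- and postintervention". Study Design ties these occasions to the workshop and to effectiveness: "Participants will complete measures before and after the workshop to assess the treatment effectiveness, as well as a 6-week follow-up". The design is within-subject, with no comparison group.

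The only length given is that of the existing manual: "A 3-day manualized version of the CBDMHI intervention is available in English, Haitian Kreyol, and Nepali". The Intervention section leaves the Australian length open: "The CBDMHI will be modified in content and length based on the local communities’ needs and availability".

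Planned Data Analysis applies one-way repeated measures ANOVAs to the phase 3 outcomes "to identify any changes in pre- and postintervention outcomes, and whether those changes were maintained up to 6 weeks". Mixed models are an option, and the reliable change index follows wherever scores are found to change over time. No section shortens the K10 recall period at the second assessment or treats the K10 differently from the other scales.

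**The concern.** One description of the analysis covers scales that behave differently in time. Preparedness and help-seeking intention, as the protocol describes them, are ratings of the respondent's present state, and asking again straight after a workshop is sensible. The K10 is a report on the past 4 weeks. Asked again a few days later, it returns largely to the days already reported at baseline.

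The planned wording takes pre-to-post as the change and 6 weeks as the test of whether it lasted. For the K10 after a short workshop this is the wrong way round, because the 6-week value is the first one whose recall window lies after the intervention.

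Two misreadings are at stake. A flat pre-to-post K10 could be reported as no effect on distress, when the scale had little chance to register one. A fall could be reported as benefit when it reflects how people felt in the room, what they expected, or answering the same items twice. With no control group these cannot be separated, and the reliable change index could then label such a fall clinically meaningful.

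**Working it through.** The protocol gives no effect size, standard deviation, alpha or power for the K10, so there is no stated figure to reproduce. The check has three steps.

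**Inputs from the protocol.** Recall window of 4 weeks = 28 days (Psychological Distress). Assessments before, at the end, and 6 weeks = 42 days later (Measures). Stated length of 3 days (section on the CBDMHI), with the adapted length open (Intervention). Up to 20 participants planned (Proposed Sample); 10 took part (Results).

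**Step 1: overlap of recall windows.** For *d* days between two K10 assessments, shared fraction = max(0, 28 − *d*)/28.

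| Days between assessments | Shared days | Share |
|---|---|---|
| 1 | 27 | 27/28 = 96% |
| 3 | 25 | 25/28 = 89% |
| 7 | 21 | 21/28 = 75% |
| 14 | 14 | 14/28 = 50% |
| 21 | 7 | 7/28 = 25% |
| 28 or more | 0 | 0% |

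Most of the window is repeated whenever the interval is under 14 days. A K10 taken as the workshop ends covers no later day, whatever *d* is. At 6 weeks the window starts on day 42 − 28 = 14 after completion, so it lies wholly after the workshop and shares nothing with baseline.

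**Step 2: attenuation.** Assume that recall days count equally and that a benefit *D* starts in full on the first day and lasts. The score at completion then registers min(*d*, 28)/28 of *D*. For 3 days this is 3/28 = 10.7%, so a true 0.5 SD would appear as 0.107 × 0.5 ≈ 0.05 SD. The remaining 89.3% would appear between completion and 6 weeks, the interval that the plan describes as maintenance. For 14 days the registered share is 50%.

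**Step 3: illustrative power.** Two-sided paired t-test, assumed alpha 0.05, assumed full standardised changes dz of 0.5, 0.8 and 1.0, each multiplied by min(*d*, 28)/28.

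| n | Contrast | dz 0.5 | dz 0.8 | dz 1.0 |
|---|---|---|---|---|
| 10 | pre to post, 3 days | 0.053 | 0.057 | 0.061 |
| 10 | pre to post, 14 days | 0.109 | 0.205 | 0.293 |
| 10 | baseline to 6 weeks | 0.293 | 0.616 | 0.803 |
| 20 | pre to post, 3 days | 0.056 | 0.065 | 0.074 |
| 20 | pre to post, 14 days | 0.186 | 0.397 | 0.565 |
| 20 | baseline to 6 weeks | 0.565 | 0.924 | 0.989 |

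At 3 days the power is close to the 5% false-positive rate. Step 3 holds the standard deviation of the change fixed. If overlapping windows make the two scores more alike, that standard deviation shrinks and the loss of power is smaller. Step 1 needs only the recall window and the interval.

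**The case against.** **The length is not fixed.** The 3-day figure belongs to the existing manual, and the protocol allows both length and timing to be adapted to local availability. Sessions spread over several weeks would reduce the overlap, to nothing at 28 days. This stands, and the percentages must be read as conditional on the interval. It does not change the fact that a K10 taken at completion covers no later time.

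**A reader might infer that a real improvement seen only at 6 weeks would be discarded.** The protocol does not support this. It states no rule that the 6-week comparison depends on a pre-to-post change. With the three occasions in Measures, the repeated measures ANOVA already uses the 6-week value, and the reliable change index is tied to change across time points generally. The problem is which contrast is presented as the effect.

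**A reader might also infer that the immediate K10 cannot show anything.** That goes too far. The model gives attenuation, not zero, and it rests on equal weighting of days and an immediate, constant benefit, neither of which the protocol states. Scores can also move for other reasons, which is itself part of the difficulty.

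**The coping items** have a frequency format that might suggest the same problem, but the protocol gives no recall period for them, so no error can be shown.

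**The study is a small uncontrolled pilot.** Adaptation, acceptability and feasibility lead its aims, effectiveness is called preliminary in Study Design, and no primary criterion rests on the K10. This stands and limits the severity. Even the clean contrast has power of only 0.29 at n = 10 for an assumed dz of 0.5.

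**Conclusion.** The point holds in conditional form. The protocol itself fixes the recall period, the assessment times and the framing of change and maintenance, and for the K10 these do not fit together. When the first two assessments are less than 14 days apart, more than half of the second recall window repeats the first, and 89% does so at the stated 3 days. The attenuation to about 11% and the power figures are illustrations resting on the assumptions given with them.

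A pre-to-post null on the K10 should therefore not be taken as absence of effect, nor a fall as evidence of one. The outcome as a whole is not lost, since the overlap-free 6-week value is already part of the design. Severity is moderate: interpretation of one outcome in a pilot is affected, and rewording the analysis corrects it.

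**What to change.** In Planned Data Analysis, for the K10 only:

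- Name baseline to 6 weeks as the effect contrast.
- Report the end-of-workshop K10 descriptively, giving the actual number of days between the two assessments and the resulting share of overlapping recall.
- Apply the reliable change index to baseline to 6 weeks.
- Do not describe the 6-week K10 as showing whether an earlier change was maintained.

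No new data are needed. According to Results, follow-up has already been collected, so the change should be dated and justified by the recall period, independently of the observed scores.

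The cost is one fewer K10 contrast and reliance on the 6-week return. Those forms are sent out and posted back, whereas baseline is completed in person, so non-return and the change of mode should be stated beside the result. The new contrast removes the recall overlap; it does not supply a control group.
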